### Sample size

Given that the intervention arm includes several new steps aimed at better tailoring fluid administration, we expect a further decrease in the use of fluids. Based on ANDROMEDA-SHOCK data, this new algorithm could reduce fluid administration in at least 60% of these patients. Previous studies have shown that a reduction in fluid administration is associated with better outcomes. Thus, we estimate a 6% absolute reduction in mortality. The estimates of the number of days needing life support truncated at 28 days and the length of hospital stay in the Control Group were based on data from the ANDROMEDA-SHOCK Control Group.

For the Control Group, we assumed a 28-day mortality of 39%, number of days needing life support truncated in 28 days among survivors of 5.6 (standard deviation [SD], 6.7) and a length-of-hospital stay truncated in 28 days among survivors of 15.6 days (SD, 10.1). We considered that the experimental group treatment would reduce mortality to 33%, shorten the number of days of life support use among survivors to 4.3 (SD, 6.2) and shorten the length of hospital stay among survivors to 14 days (SD, 9.9).The length of hospital stay and the number of days needing life support were simulated assuming a beta-binomial distribution within 28 days via parameters acquired in the ANDROMEDA-SHOCK trial.^7^

Using the win ratio method with the three components listed above, with 1,500 patients enrolled, the trial will have a power of 88% to show superiority in the win ratio outcome for a two-sided α of 0.05. The study power was estimated based on 1,000 replications.

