#### Baseline patient characteristics

The baseline characteristics recorded during the trial will be presented in table 1 (dummy).

**Table 1 t1:** Patient characteristics at randomization

Characteristic	CRT-P guided resuscitation (n = xxx)	Usual care (n = xxx)
Demographics		
Age (years)	xx (xx – xx)	xx (xx – xx)
Sex		
Men	xx (xx)	xx (xx)
Women	xx (xx)	xx (xx)
Body mass index	xx (xx – xx)	xx (xx – xx)
APACHE II	xx (xx – xx)	xx (xx – xx)
Baseline SOFA score	xx (xx – xx)	xx (xx – xx)
Charlson Comorbidity Index	xx (xx – xx)	xx (xx – xx)
Time from hypotension to antibiotic start (hours)	xx (xx – xx)	xx (xx – xx)
Time from meeting entry criteria to randomization (hours)	xx (xx – xx)	xx (xx – xx)
Comorbidities		
Hypertension	xx (xx)	xx (xx)
Diabetes	xx (xx)	xx (xx)
Chronic obstructive pulmonary disease	xx (xx)	xx (xx)
Chronic renal disease	xx (xx)	xx (xx)
Hematological cancer	xx (xx)	xx (xx)
Nonhematological Cancer	xx (xx)	xx (xx)
Immunosuppression	xx (xx)	xx (xx)
Liver disease	xx (xx)	xx (xx)
Heart failure	xx (xx)	xx (xx)
Coronary artery disease	xx (xx)	xx (xx)
Source of infection		
Abdominal	xx (xx)	xx (xx)
Lung	xx (xx)	xx (xx)
Urinary tract	xx (xx)	xx (xx)
Soft tissues	xx (xx)	xx (xx)
Primary bacteremia	xx (xx)	xx (xx)
Other	xx (xx)	xx (xx)
Unknown	xx (xx)	xx (xx)
Characteristics at randomization		
Resuscitation fluids at randomization (mL)	xx (xx – xx)	xx (xx – xx)
Supplemental oxygen	xx (xx)	xx (xx)
Mechanical ventilation		
Invasive	xx (xx – xx)	xx (xx – xx)
Noninvasive	xx (xx – xx)	xx (xx – xx)
Lactate > 4.0 mmol/L	xx (xx)	xx (xx)
Lactate level (mmol/L)	xx (xx – xx)	xx (xx – xx)
Mottling score		
Capillary refill time (seconds)	xx (xx – xx)	xx (xx – xx)
Norepinephrine dose* (mcg/kg/minute)	x.xx (x.xx - x.xx)	x.xx (x.xx - x.xx)
Vasopressin use	xx (xx)	xx (xx)
Venous-to-arterial carbon dioxide difference (mmHg)	xx (xx – xx)	xx (xx – xx)
Central venous oxygen saturation	xx (xx – xx)	xx (xx – xx)

CRT-P - Intervention Group; APACHE - Acute Physiology and Chronic Health Evaluation; SOFA - Sequential Organ Failure Assessment. * Expressed as a norepinephrine base.

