#### Tertiary outcomes

The tertiary clinical outcomes are as follows: all-cause mortality within 90 days after randomization, length of hospital stay, length of ICU stay, time to cessation of vasopressor support, time to cessation of mechanical ventilation (MV), time to cessation of renal replacement therapy (RRT), vasopressor support-free days, MV-free days, RRT-free days, variation in Sequential Organ Failure Assessment (SOFA) score, variation in creatinine-based Kidney Disease: Improving Global Outcomes (KDIGO) stage, volume of resuscitation fluids, net fluid balance, evolution of CRT, evolution of lactate levels, evolution of central venous pressure (CVP), evolution of central venous oxygen saturation (ScvO2), and evolution of the central venous to arterial carbon dioxide difference (delta pCO2(v-a)).

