## Tertiary outcome analysis

All-cause mortality within 90 days will be assessed with a Cox proportional hazard model adjusted for the baseline APACHE II score. The effects on the length of hospital stay, length of ICU stay, time to cessation of vasopressor support, time to cessation of MV, and time to cessation of RRT will be estimated with generalized linear models using the distribution that best fits the data and adjusted for the baseline APACHE II score. Vasopressor support-free days, MV-free days, and RRT-free days will be assessed with a cumulative logistic model adjusted for the baseline APACHE II score.^15,16^Effects on repeated measures of organ dysfunction at 7 days (SOFA), CRT and lactate levels will be analyzed via mixed models with patients as random effects, treatment groups as fixed effects, and treatment‒time interactions while adjusting for the baseline SOFA score. The effect will be presented as the difference between the slopes of the groups or, equivalently, the treatment‒time interaction. The effects on other continuous outcomes, such as length of hospital stay and length of ICU stay, will be calculated with generalized linear models with the distribution that best fits the data. Adjustments for baseline APACHE II score, evolution volume resuscitation fluid, and net fluid balance will also be assessed with generalized linear models with the distribution that best fits the data and no adjustments for baseline covariates. For all continuous outcomes for which we will define the best distribution at the time of statistical analysis, the criteria will involve assessing which distribution best fits the data via residual and QQ-plot analysis, which will be published in the supplementary manuscript to increase transparency.

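### Fluid volume and net fluid balance are expressly analysed without baseline adjustment, although APACHE II and fluids at randomization are recorded and would sharpen the estimate

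*SAP article*

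**What the plan says.** Everything here is in the SAP article.

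- **Outcomes concerned.** The list under Tertiary outcomes includes "volume of resuscitation fluids, net fluid balance".
- **Model for them.** The relevant sentence under Tertiary outcome analysis begins "Adjustments for baseline APACHE II score, evolution volume resuscitation fluid, and net fluid balance will also be assessed with generalized linear models" and ends "with the distribution that best fits the data and no adjustments for baseline covariates".
- **Other tertiary models in that section.** 90-day mortality gets a "Cox proportional hazard model adjusted for the baseline APACHE II score". Hospital stay, ICU stay and the times to cessation of each support are modelled "using the distribution that best fits the data and adjusted for the baseline APACHE II score". Support-free days are also adjusted for APACHE II. SOFA, CRT and lactate are adjusted for baseline SOFA.
- **Secondary outcomes.** All three are adjusted for APACHE II.
- **Baseline data.** Table 1 has a row for APACHE II and a row that begins "Resuscitation fluids at randomization (mL".
- **Role of fluids.** Under Sample size, the authors write "we expect a further decrease in the use of fluids", and from this they argue to a 6-point absolute reduction in mortality (39% to 33%).
- **Status.** Under Statistical analysis principles, tertiary outcomes carry no p values and are called exploratory, but 95% confidence intervals are given for all effect estimates.

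**The concern.** The plan adjusts most of what it models for a baseline severity score, then rules out any covariate for two outcomes where a closely related baseline quantity has been collected. Fluid already given by randomization may well predict fluid given afterwards, and severity may predict both. No reason for the exception is stated.

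Precision and consistency are at stake. These two outcomes show whether the strategy changed fluid use, which is the route by which the sample size section expects mortality to fall. Because tertiary outcomes have no p values, the reader will judge that question from the estimate and its interval alone, and interval width is what adjustment improves.

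The sentence is also hard to read. It names an APACHE II adjustment at the start and excludes baseline covariates at the end, so an analyst needs to know which instruction applies to which outcome.

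**Working it through.** **Step 1: what the sentence means.** There are two ways to read it.

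- *Literally:* an adjustment for APACHE II stands in a list with fluid volume and net fluid balance, as if it were a third outcome to be modelled. That makes no sense.
- *With one full stop moved:* the phrase about APACHE II closes the preceding sentence, which deals with hospital and ICU stay. That agrees with the earlier sentence in the same section that already adjusts those two outcomes for APACHE II. The next sentence then starts with the fluid outcomes and gives them no covariates.

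The second reading is the probable one. It removes the apparent contradiction and leaves the fluid outcomes expressly unadjusted.

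**Step 2: is the exception shared?** Adjusted: three secondary outcomes, 90-day mortality, lengths of stay, times to cessation, support-free days, SOFA, CRT and lactate. No named model or covariate: KDIGO variation, CVP, ScvO2 and the carbon dioxide difference. Expressly unadjusted: the two fluid outcomes.

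**Step 3: size.** The article gives no SD, effect or power for the fluid outcomes, so there is no stated figure to reproduce. Nor does it give the correlation r between baseline covariates and outcome (the multiple correlation if two covariates are used), so r is assumed over a range. In a linear model with randomised groups:

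- variance, adjusted / unadjusted = 1 − r²
- interval width, adjusted / unadjusted = √(1 − r²)
- unadjusted sample with the same precision = 1,500 / (1 − r²), where 1,500 is the planned enrolment

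| r (assumed) | 1 − r² | Width ratio | Interval narrower by | Equivalent N |
|---|---|---|---|---|
| 0.1 | 0.99 | 0.995 | 0.5% | 1,515 |
| 0.2 | 0.96 | 0.980 | 2% | 1,562 |
| 0.3 | 0.91 | 0.954 | 5% | 1,648 |
| 0.4 | 0.84 | 0.917 | 8% | 1,786 |
| 0.5 | 0.75 | 0.866 | 13% | 2,000 |
| 0.6 | 0.64 | 0.800 | 20% | 2,344 |

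For example, at r = 0.5: 1 − 0.25 = 0.75; √0.75 = 0.866; 1,500 / 0.75 = 2,000.

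These are approximations. The plan chooses the distribution of each generalized linear model from the data, and the formulas are exact only for the linear case.

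**The case against.** The strongest reply is that nothing here is wrong. The rule for the fluid outcomes is prespecified, an unadjusted comparison in a randomised trial is unbiased, and its interval already allows for chance imbalance in earlier fluids. The outcomes are exploratory, and no decision in the SAP depends on them. The gain rests on a correlation that nobody has supplied, and at r = 0.1 or 0.2 it is negligible. Adjustment also has a small price: patients without a baseline value would drop out of a complete-case model, and the section on analysis populations gives no rule for missing covariates.

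All of that stands, and it limits the point to efficiency and consistency. It does not explain why a quantity already collected is left out, and the missing-value problem is easily handled.

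A reader might infer three stronger things that the document does not support:

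- **That the plan contradicts itself on the fluid outcomes.** The misplaced full stop is the likelier explanation.
- **That these are the only outcomes analysed without adjustment.** Several tertiary outcomes have no stated model at all, so one can say only that these two are expressly unadjusted.
- **That the fluid comparison is biased, or that the trial's conclusion is weakened.** Randomisation protects the first, and the conclusion rests on the primary outcome.

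**Conclusion.** The point holds as a minor improvement. Once the punctuation is repaired, the plan still denies baseline adjustment to fluid volume and net fluid balance without a reason, against its usual practice and with suitable covariates to hand. The analysis as planned is valid but less precise than it could be.

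The loss depends on an assumed correlation: negligible near 0.1, modest near 0.3 and worthwhile near 0.5. This rests on the linear-model approximation and on reading the Table 1 row as the volume received up to randomization. No figure in the document changes.

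**What to change.** 1. Attach the opening phrase about APACHE II adjustment to the preceding sentence on hospital and ICU stay.
2. Replace the rest of the sentence with wording such as:

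> Resuscitation fluid volume and net fluid balance will be analysed with generalized linear models adjusted for baseline APACHE II score and the volume of resuscitation fluids at randomization. Missing baseline values will be filled by single imputation without reference to treatment group or outcome.

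3. Name the effect measure to be reported if a non-identity link is chosen.

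If the authors prefer to keep these outcomes unadjusted, one sentence giving the reason would do.

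The cost is a few lines of text before the database is locked. No new data are needed, since both covariates are already in Table 1. The only burdens are the handling of missing baseline values and, under a non-identity link, stating what the adjusted estimate measures.

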## Heterogeneity of treatment effects

We will assess whether treatment varies according to baseline patient characteristics via conventional subgroup analysis and risk modeling.^17^

The effect of the treatment on the primary hierarchical composite outcome will be assessed according to the following subgroups: age (< or ≥ 65 years), APACHE II score (< or ≥ 25 points), SOFA score (< or ≥ 10 points), baseline lactate level (< or ≥ 4mmol/L), baseline CRT (< or ≥ 3 seconds), origin of septic shock (pulmonary, abdominal, urinary, soft tissue *versus* bacteraemia *versus* other), and invasive mechanical ventilation at inclusion.

We will assess the heterogeneity of treatment effects by risk modeling through analysis of the win ratio according to quintiles of APACHE-2 scores.^17^

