### Statistical analysis principles

We will report two-sided p values for the primary outcome main analysis. If the experimental group strategy is superior to the Control Group for the primary outcome (p value < 0.05), we will test the treatment effect on the secondary outcomes in a hierarchical fashion at a significance level of 0.05. Ninety-five percent confidence intervals will be presented for all effect estimates. P values will not be presented for tertiary outcomes or other analyses. Owing to the risk of Type I error from numerous comparisons, the results for tertiary outcomes and other analyses should be considered exploratory.

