## Preplanned *post hoc* analysis

Considering the granularity of the data registered, multiple preplanned post hoc analyses will be performed from the ANDROMEDA-SHOCK-2 trial database. Our assessments include the following: an assessment of the evolution of fluid responsiveness over time and according to cumulative fluids administered; an assessment of the prevalence of use, achievement and impact of the three hemodynamic interventions (DAP test, MAP test, and inodilator test) on tissue perfusion; a Bayesian reanalysis of the primary outcome; a per-protocol analysis; an analysis of the kinetics of CRT evolution during the resuscitation timeframe; an assessment of the need for echocardiography; an assessment of the prevalence and patterns of cardiac dysfunction; a VExUS assessment after the study period and its relationship with acute kidney injury; and an assessment of the interactions between study groups, comparing high *versus* low recruiters and the first 25% *versus* the last 25% of patients recruited. We plan to carry out effect-modeling analysis via machine learning models to assess the effects of the experimental *versus* control strategies on 28-day mortality.^18^

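### The plan sets out to assess whether the treatment effect varies but specifies only within-level win ratios, so no between-level contrast is planned and chance differences between intervals can easily be misread as effect modification

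*SAP article*

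**What the plan says.** The section Heterogeneity of treatment effects opens with its aim: "We will assess whether treatment varies according to baseline patient characteristics via conventional subgroup analysis and risk modeling". Two outputs follow.

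- Subgroups: "The effect of the treatment on the primary hierarchical composite outcome will be assessed according to the following subgroups". Seven factors are listed. Six have two levels (age, APACHE II, SOFA, lactate, capillary refill time, invasive ventilation) and one, the origin of septic shock, has several.
- Risk modeling: "We will assess the heterogeneity of treatment effects by risk modeling through analysis of the win ratio according to quintiles of APACHE-2 scores".

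No interaction term, ratio of win ratios, trend or heterogeneity statistic is named.

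Statistical analysis principles sets the general reporting rules: "Ninety-five percent confidence intervals will be presented for all effect estimates", but "P values will not be presented for tertiary outcomes or other analyses". It adds that "the results for tertiary outcomes and other analyses should be considered exploratory".

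Interactions appear in two other places. Tertiary outcome analysis names a treatment-by-time interaction for repeated measures. Preplanned post hoc analysis lists "an assessment of the interactions between study groups", for high versus low recruiters and for the first versus last quarter of recruitment. Neither covers the baseline subgroups.

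**The concern.** Whether an effect varies is a question about a difference between levels. A win ratio and its interval inside one level do not measure that difference. With one interval per level and no p values, the most visible feature of the display is which intervals cross 1, and that depends heavily on the size of each subgroup even when the effect is the same throughout.

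The win ratio makes the gap more important. It comes from comparing all pairs, with a bootstrap interval, and not from a regression with a ready interaction term. If the contrast is not named in advance, the analyst must choose one after seeing the data, which the Introduction says the SAP exists to prevent. What is at stake is how an exploratory display is read. The trial's main conclusion is not at stake.

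**Working it through.** **Inputs from the SAP article.** Sample size: "with 1,500 patients enrolled, the trial will have a power of 88% to show superiority in the win ratio outcome for a two-sided α"; the level is 0.05. Also control and experimental mortality of 39% and 33%; life-support days in survivors of 5.6 (SD 6.7) and 4.3 (SD 6.2); hospital stay in survivors of 15.6 (SD 10.1) and 14 (SD 9.9). Allocation is 1:1, so 750 per arm.

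**Inputs assumed.** Subgroup prevalences (the article gives none), independence between splits, and a normal approximation for the log win ratio. APACHE II stratification is left out.

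**The plan's own power figure.** The trial was simulated with binary death, beta-binomial days matched to the stated means and SDs, all-pairs comparison and death-death pairs tied. This gave a win ratio of 1.32 to 1.34, a standard error of the log win ratio of about 0.068, and power of 98.7% to 99.1%. The stated 88% was not reproduced. I do not call that an error, because the exact beta-binomial parameters, the joint distribution and the strata are not given. Both power levels are carried through as a range.

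**One split, identical true effect.** Let *d* be the expected overall z-statistic: d = z(0.975) + z(power). A subgroup holding a fraction *f* of the patients has expected z of d√f, so its interval excludes 1 with probability s(f) = 1 − Φ(1.96 − d√f). The two levels are disjoint, so exactly one interval excludes 1 with probability s(f)[1 − s(1−f)] + s(1−f)[1 − s(f)].

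- Power 88%: d = 1.960 + 1.175 = 3.135. For f = 0.5, d√f = 2.217 and s = 0.601. Discordance = 2 × 0.601 × 0.399 = 0.48.
- Power 99%: d = 1.960 + 2.326 = 4.286. For f = 0.5, d√f = 3.031 and s = 0.858. Discordance = 2 × 0.858 × 0.142 = 0.24. Direct simulation from the planning inputs gave 0.25 to 0.28.
- Uneven split 30:70: 0.55 at 88% power and 0.36 at 99%.

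The contrast, the difference in log win ratio divided by its standard error, gave a false signal in 4.7% to 5.5% of simulated trials for two halves.

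**At least one of six two-level splits.** The splits divide the same patients, so they share the overall estimate, and 1 − (1 − p)⁶ does not apply to discordance. I drew the overall z once per trial and an independent standard normal e for each split, with level statistics √f·z + √(1−f)·e and √(1−f)·z − √f·e.

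| Overall power | Even splits | Prevalences 30-50% | Six contrasts |
|---|---|---|---|
| 99% | 54% | 67-69% | 26-27% |
| 88% | 84% | 88% | 26-27% |

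The last column agrees with 1 − 0.95⁶ = 0.265. Here the product rule does apply, because the contrasts depend only on the independent e terms.

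**Quintiles.** At 88% power each fifth has s(0.2) = 0.288. A mixed picture across the five intervals arises with probability 1 − 0.288⁵ − 0.712⁵ = 0.82. Simulation from the planning inputs gave 93% to 94%. A heterogeneity statistic across the five gave a false signal in 5.0% to 5.1%.

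**The case against.** The plan is silent on a contrast; it does not forbid one. The phrase about conventional subgroup analysis cites a source that is not shown and may imply an interaction analysis, and the promise of intervals for all effect estimates would cover a contrast if one were computed. The article is condensed and its supplementary tables are not shown. These points limit how strongly the matter can be put, but the text shown still fixes within-level estimates and no measure of their difference, and the general rule would suppress an interaction p value.

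A reader might infer that the plan will judge heterogeneity by which intervals exclude 1. It does not say so. The discordance rates describe a reading that the display invites, not a decision rule in the plan.

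A reader might also infer that the analysis cannot answer its own question. That is too strong. The levels of a factor are disjoint groups, so an approximate difference in log win ratio can be worked out from two reported estimates and intervals.

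Setting the six-split discordance rate against 5% would mix units, because the first is per trial and the second per split. Like for like, it is 24-48% against 5% for one even split, and 54-88% against about 27% for six.

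Finally, the analyses are labelled exploratory and the trial's conclusion rests on the intention-to-treat primary analysis. That lowers the stakes. The label addresses multiplicity, however, and does not turn a within-level interval into an estimate of a between-level difference.

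**Conclusion.** The point holds as a modest improvement to the plan. The heterogeneity section asks whether the effect varies and, as written, plans no estimate of that variation for the baseline subgroups or the APACHE II quintiles. With an identical effect in all patients, discordant intervals are common: about 24% to 48% of trials for a single even split, against 5% for a contrast, and about 54% to 88% for at least one of six splits, against about 27%.

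The range reflects overall power of 99% or 88% and, for six splits, even splits or assumed prevalences of 30-50%. It also rests on independent splits, which is doubtful for two overlapping severity scores such as APACHE II and SOFA. The direction does not depend on these choices, but the exact size does. The primary result is not affected.

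**What to change.** Add to Heterogeneity of treatment effects that:

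- for each two-level factor, the ratio of win ratios (difference in log win ratio) will be reported with a bootstrap 95% confidence interval;
- infection source will use contrasts with a named reference level, and APACHE II quintiles a trend in log win ratio;
- any exploratory statement on heterogeneity will rest on these contrasts, with a note that several are examined without multiplicity control, so about one trial in four would show at least one false signal among six.

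This keeps the rule against p values and uses the bootstrap method already planned for the primary analysis. The cost is a short addition to the text, slightly more analysis and an extra column wherever subgroup results are shown. The drawback is wide intervals. With an overall standard error of 0.0676, an even split gives a standard error of 2 × 0.0676 = 0.135 for the difference. An observed ratio of win ratios of 1 would then carry an interval of about 0.77 to 1.30 (exp(±1.96 × 0.135)). That shows readers how little the subgroups can say.
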